## Abstract

**Background:**

It has been reported that following rehabilitation, only 7% of stroke survivors are able to walk at a level commensurate with community participation. Previous research indicates that treadmill and overground walking training can improve walking capacity in people living in the community after stroke. The main objectives of the AMBULATE trial are to determine (i) whether a 4-month treadmill walking program is more effective than a 2-month program, compared to control, in improving walking capacity, health and community participation and (ii) the "threshold" walking speed that results in sufficient walking capacity that makes walking self-sustaining.

**Methods/Design:**

A prospective randomised controlled trial of unsupported treadmill training with a 12 month follow-up with concealed allocation and blinded assessment will be conducted. 210 community-dwelling people after stroke who are able to walk independently but slowly will be recruited and randomly allocated to either a 4 month training group, 2 month training group or the control (no intervention) group. Intervention for the two training groups will occur 3 days per week for 30 minutes each session. Measurements of walking, health and community participation will be taken at baseline, 2 months, 4 months, 6 months and 12 months. This study has obtained ethical approval from the relevant Human Research Ethics Committees.

**Discussion:**

By improving stroke survivors' walking ability, it is likely also to improve their general wellbeing by promoting better health and greater community participation. Furthermore, if stroke survivors can reach a point where their walking and community participation is self-sustaining, this will reduce the burden of care on family and friends as well as the economic burden on the health system. Given the major demographic shift in developed nations involving significant growth in the aged population, this research will make an important evidence-based contribution to the promotion of healthy ageing.

**Trial registration:**

This trial is registered with the Australian New Zealand Clinical Trials Registry, (ACTRN012607000227493)

## Background

Walking is an important human activity which enables us to be productive and participative members of a community. Normal walking speed for older persons is 1.3 m/s [1] and walking capacity measured by the distance covered in 6 minutes is 576 m for men and 494 m for women [2]. After stroke, although the majority of patients leave rehabilitation with some level of independent walking, many have residual walking disabilities. Walking speed of community-dwelling people after stroke has been reported to be around 0.5 m/s with studies reporting a range between 0.3 and 0.8 m/s [3-7]. Walking capacity has also been found to be markedly reduced with 6-minute distance being reported as around 250 m ranging between 40 and 400 m [8,9]. This reduction in walking speed and capacity results in major limitations in community participation. For example, Hill and colleagues [3] found that many individuals after stroke could not walk fast enough to cross the road safely or far enough to do the shopping. The consequence of poor walking ability is widespread, affecting the person and their family and friends. Poor walking ability has been found to reduce quality of life with a reduction in participation in activities outside the home and therefore social isolation. In particular, patients fear dependency more than anything else after a stroke and the ability to walk independently has been found to provide the greatest protection against dependency [10]. A community ambulator is less dependent on family and friends not only for assistance with household tasks but also for assistance with community participation.

One of the most promising ways of increasing walking ability post-discharge from rehabilitation after stroke is to use treadmill training. Although the Cochrane review on treadmill training [11] suggests that *supported *treadmill walking is somewhat effective in improving walking (increase in walking speed 0.24 m/s, 95% CI -0.19 to 0.66) in inpatients that can already walk, the review did not examine *unsupported *treadmill training when used post-discharge as a means of improving community ambulation. There have been several uncontrolled trials which suggest that *unsupported *treadmill training is effective. For example, Macko et al [12,13] demonstrated an increase in fitness after a 6-month treadmill training program in community-dwelling ambulatory people after stroke. Smith et al [14,15] demonstrated an increase in strength and a decrease in spasticity after a 3-month program of treadmill training while Silver et al [16] demonstrated an increase in walking speed. In a previous randomised controlled trial of *unsupported *treadmill training in community-dwelling people after stroke, it was demonstrated that a 4 week program is effective in improving walking speed and distance covered in six minutes [17]. However, the gains in 6-minute distance were not maintained at follow-up 3 months later (Figure 1).

**Figure 1 F1:**
[figure not shown]
**Improvements of 80 m in 6-min distance following a one-month treadmill and overground walking program (solid = experimental, dotted = control) with subsequent relapse over three months (from Ada et al **[17] with permission).

In summary, the main objectives of the AMBULATE trial are to determine (i) whether a 4-month treadmill and overground walking program is more effective than a 2-month program, compared to control, in improving walking capacity, health and community participation and (ii) the "threshold" walking speed that results in sufficient walking capacity that makes walking self-sustaining.

## Methods/Design

A prospective, randomised controlled trial will be carried out (Figure 2). It will include concealed randomisation, blinded assessment and intention-to-treat analysis. 210 participants will be recruited and randomly allocated into either Group A (walking training 3 times per week for 4 months), Group B (walking training 3 times per week for 2 months) or Group C (no active intervention). Outcome measures will be collected at baseline, 2 months, 4 months, 6 months and 12 months. Both data collection and data analysis will be completed by a researcher who is blinded to group allocation. The study has obtained ethical approval from the appropriate Human Research Ethics Committees.

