### Measurement

Since the main aim the study is to improve community ambulation, the primary outcome will be walking capacity measured as the distance covered during the 6-minunte walk test at 12 months. Given the hypothesis that improving walking capacity will directly lead to improvements in health and community participation, the secondary outcomes measures will include measures of health and community participation as well as a measure of walking quality.

Therefore, the outcome measures will be:

• Walking

Walking capacity will be assessed using the 6-minute Walk Test (distance covered in 6 min). Walking quality will be assessed using the 10-metre Walk Test (speed, stride length, cadence).

• Health

Health will be assessed by recording number of falls, number of readmissions to hospital, number of comorbidities, number of visits to the doctor, and quality of life (Euroqol EQ-5D score).

• Community participation

Community participation will be assessed using a self-efficacy questionnaire about walking ability, based on the Falls Efficacy Scale [19] and the Adelaide Activities Profile [20].

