### Sample size

210 participants will be recruited. The sample size has been calculated to reliably detect a treatment effect size of a 50 m difference in walking capacity with 80% power at a two-tailed significance level of 0.05 on any pairwise comparison. This effect size has been derived from the walking capacity of a population of community-dwelling stroke patients who took part in the previous treadmill walking program [17]. On entry to this randomised controlled trial, the distance walked in 6 minutes was 280 (SD, 100) m using the same measurement procedure to the present proposal. The smallest number of participants to detect a 50 m difference between two groups estimated from independent samples is 63 participants per group, i.e., 189 participants in total. On the assumption that about 10% of the participants may drop out during the course of the study, we have set a target of 210 participants in total.

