### Statistical analysis

The variables that reflect walking capacity, community participation and quality of life will be analysed by pairwise comparisons between the three groups using the Students' t-test, or Wilcoxon's rank-sum test if it is clearly not normally distributed.

The other health variables: number of falls, number of readmissions to hospital, comorbidities, and number of visits to the doctors will be expressed as a proportion of events per person and analysed by pairwise comparisons between the three groups using the Chi square test.

To ascertain the threshold of post-intervention walking speed that results in the maintenance of 80% of predicted 6-min distance at 12 months, receiver operating characteristic (ROC) curves will be constructed. Youden's Index will be used to determine the cut-off point for walking speed at the end of the programs that gives the best combination of specificity and sensitivity.

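### The article promises intention-to-treat, but the only analysis it names for the 12-month primary outcome is a two-sample test that, as written, reduces to available cases

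*Protocol article*

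**What the plan says.** Four statements in the protocol article bear on this point.

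- **Principle (Methods/Design):** "It will include concealed randomisation, blinded assessment and intention-to-treat analysis".
- **Schedule (Methods/Design):** "Outcome measures will be collected at baseline, 2 months, 4 months, 6 months and 12 months".
- **Primary outcome (Measurement):** "the primary outcome will be walking capacity measured as the distance covered during the 6-minunte walk test at 12 months".
- **Analysis (Statistical analysis):** one rule covers quality of life, walking capacity and community participation alike. It reads: "will be analysed by pairwise comparisons between the three groups using the Students' t-test, or Wilcoxon's rank-sum test". The rank-sum test is reserved for data that are plainly non-normal.

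The Sample size section adds the expected loss: "On the assumption that about 10% of the participants may drop out during the course of the study". It finds 63 per group (189 in all) and sets the recruitment target at 210.

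The article does not say how a randomised participant without a 12-month distance enters the primary comparison. It does not say that such participants are excluded either.

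**The concern.** A two-sample test at one time point has nothing to work with for a person who has no value at that time point. On the plan's own dropout figure, about 21 randomised participants would contribute nothing to the primary comparison unless some further rule brings them in. The named test also ignores baseline distance and the three intermediate distances, which carry information about where a dropout was heading.

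Uneven loss is plausible in this design. One arm trains three times a week for 4 months, one for 2 months, and one has no active intervention. Participants are within 5 years of a first stroke, and falls and hospital readmissions are themselves outcomes, so events that reduce walking and also end participation are foreseeable. If such losses differ between arms, comparing the people who remain no longer compares the groups as randomised. That comparison is what the intention-to-treat statement is meant to protect.

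**Working it through.** **Step 1. Reproduce the plan's figures.** Inputs from the Sample size section: "50 m difference in walking capacity with 80% power at a two-tailed significance level of 0.05 on any pairwise comparison", and an SD of 100 m taken from entry to the earlier trial ("the distance walked in 6 minutes was 280 (SD, 100) m").

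- Per group: n = 2 × (1.960 + 0.842)² × 100² / 50² = 62.8, so 63.
- Three groups: 3 × 63 = 189.
- Allowing for 10% loss: 189 / 0.90 = 210, or 70 per group.

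All three figures reproduce. (The exact t calculation gives 64 per group, and 79.5% power at 63; the difference is immaterial.) The expected number without a 12-month distance is 210 − 189 = 21.

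**Step 2. Bias of an available-case comparison.** Let d be the proportion lost in an arm and g the amount by which the dropouts' mean 12-month distance would fall below the completers' mean. The completers' mean then exceeds the whole-arm mean by d × g. The error in the difference between two arms is

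bias = d₁g₁ − d₂g₂, which is g × (d₁ − d₂) when g is the same in both.

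The documents give only an overall dropout of about 10%. The arm-specific rates and the gaps below are assumptions.

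| Dropout, arm 1 vs arm 2 | Gap g | Bias | Share of 50 m |
|---|---|---|---|
| 10% vs 10% | 50 m in both | 0 m | 0% |
| 15% vs 5% | 50 m in both | 5 m | 10% |
| 15% vs 5% | 100 m in both | 10 m | 20% |
| 10% vs 10% | 100 m vs 50 m | 0.10 × (100 − 50) = 5 m | 10% |

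The arm that loses more weak walkers looks better than it is. Heavier loss from control therefore hides benefit, and heavier loss from a training arm exaggerates it. The result depends on how the gap is defined. If the 100 m were measured from the whole-arm mean instead, the 15% versus 5% case would give 100 × (0.15/0.85 − 0.05/0.95) = 12.4 m.

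**Step 3. Power.** Suppose the earlier distances have multiple correlation R with the 12-month distance (assumed; not in the documents) and every dropout has those earlier distances, which makes this an upper bound. Then the variance of a pairwise difference is

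2 × 100² × [(1 − R²)/63 + R²/70].

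| R | Effective n per group | Power |
|---|---|---|
| 0 | 63.0 | 80.1% |
| 0.5 | 64.6 | 81.1% |
| 0.7 | 66.2 | 82.1% |
| 0.9 | 68.6 | 83.3% |
| 1 (ceiling) | 70.0 | 84.1% |

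Retaining the dropouts' information adds at most 84.1 − 80.1 = 4.0 percentage points. The case rests mainly on bias.

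**The case against.** A reader might infer that the plan commits itself to completers only, throws away the earlier distances and so fails to deliver intention-to-treat. The documents do not support that.

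- **No exclusion is stated.** The Statistical analysis section names a test, not an analysis set. Intention-to-treat, in the sense of analysing people in their allocated group, is compatible with a t-test, and a t-test can follow imputation.
- **The sample size is not evidence of a completers' analysis.** Allowing for lost information is standard and is done correctly here. A trial that planned imputation would do the same.
- **The earlier visits may well be analysed.** The pairwise comparisons are not restricted to 12 months. What can be said is only that the 12-month test makes no use of the earlier distances.
- **Dropout related to walking is not enough to cause bias.** As Step 2 shows, equal dropout of the same kind leaves the difference unbiased even if dropouts walk less. The documents give no sign of what the arm-specific rates will be.
- **Missing-data rules are often left to fuller documents.** The full protocol and any statistical analysis plan are not shown, so the absence of such a rule in an article is not in itself a fault.

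All five points stand, and they limit the finding. They do not remove it, because the article does state its primary test. That stated choice can be judged against the data the trial will hold, and a better analysis is available from the same visits.

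**Conclusion.** The point holds as a weakness in the stated analysis; it is not a demonstrated breach of intention-to-treat. Without a further rule, the named test reduces to available cases, about 189 of 210, and leaves the baseline, 2-, 4- and 6-month distances out of the primary comparison.

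The possible bias is moderate: 5 to 10 m against a 50 m target, on assumed dropout of 5% versus 15% and a gap of 50 to 100 m between dropouts and completers. It is nil if dropout is equal and of the same kind in the arms compared. The loss of power is minor. The sample size needs no change. The change is worth making because it relies on a weaker assumption about missing data and costs little.

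**What to change.** Name as the primary analysis a likelihood-based repeated-measures model for 6-minute walk distance:

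- participants analysed in the group to which they were randomised;
- all visits (2, 4, 6 and 12 months), with baseline distance either in the outcome vector or as a covariate;
- group × visit terms, and the walking-speed matching factor used in the randomisation;
- the three 12-month pairwise contrasts as the primary estimates.

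The article does not say when dropout is expected. Someone lost before 2 months has only a baseline distance. Keeping baseline in the outcome vector retains that person in the model, whereas using it only as a covariate does not. The plan should state which is chosen.

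Add a sensitivity analysis that lets dropouts do worse than missing at random predicts, by amounts that may differ between arms. Report dropout and its reasons by arm.

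**Cost:** revised analysis wording and some programming, with no new data and no change to the 210. The downside is a model in place of a simple test, and a primary result that still rests on missing at random. Adjustment for baseline may also improve precision, by an amount that depends on a correlation the documents do not give.

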**Figure 2 F2:**
[figure not shown]
**Design of study**.

The end point of the training phase of the study for Group A will be 4 months and for Group B will be 2 months. The end point of the follow-up phases of the study will be 6 months and 12 months after admission to the study for all groups.

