### Randomisation

Randomisation will be computer-generated, independent and concealed. Participants will be recruited in cohorts of 15. Each cohort will be ranked in descending order according to comfortable walking speed over 10 m and then organized into matched triplets. The participants in each triplet will then be assigned to Group A or B or C by random allocation generated by computer in order to provide secure randomisation, concealed from the recruiter. In this way, participants will be stratified according to initial level of walking disability since this has been found to affect outcome [18].

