### Intervention

Training for both intervention groups will be based on a previously-successful treadmill walking program [17]. It will be carried out 3 times a week and the sessions will comprise 30 min of walking. Participants will receive individual training from a physiotherapist; however, there will be opportunity for social interaction since several participants will be trained concurrently. The program will be carried out in a community setting and transport will be provided if necessary. Guidelines will outline the progression of training. Information describing the specific features of the training session (such as treadmill speed, distance walked, assistance required, etc) will be recorded to monitor adherence to the guidelines and to be able to describe the intervention accurately.

Treadmill walking will be structured to increase stride length, speed, workload, and automaticity. To increase stride length, the treadmill will be run at a comfortable speed and participants will be instructed to "walk as slowly as possible". In addition, marching type steps will be included to encourage hip and knee flexion during swing phase to improve toe clearance. A metronome may also be used to decrease cadence and to encourage larger steps. When a normal step length is observed, the speed of the treadmill will be increased (until step length is compromised). Workload will then be addressed by increasing the incline of the treadmill. Finally, automaticity will promoted by presenting the participants with a concurrent cognitive task while maintaining speed and normal step length. The cognitive task may include the participant holding a conversation with the physiotherapist or may be a more structured task such as matching the word "red" with the response "yes" or the word "blue" with the response "no". During treadmill walking, attention will also be focused on alignment to help participants keep their trunk vertical.

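### Groups A and B are assigned the same programme to month 2, yet the stated unadjusted three-group tests neither pool them at that visit nor use the entry distance: an efficiency loss that is cheap to recover

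*Protocol article*

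**What the plan says.** Methods/Design defines the trained arms by duration alone: "Group A (walking training 3 times per week for 4 months), Group B (walking training 3 times per week for 2 months". Below Figure 2 it adds: "The end point of the training phase of the study for Group A will be 4 months and for Group B will be 2 months". Under Intervention, a single description covers both arms: "Training for both intervention groups will be based on a previously-successful treadmill walking program", three sessions a week of 30 minutes of walking. No difference between the arms before month 2 is described.

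Allocation is made once, at entry, within triplets matched on walking speed: "The participants in each triplet will then be assigned to Group A or B or C by random allocation". The visit schedule is: "Outcome measures will be collected at baseline, 2 months, 4 months, 6 months and 12 months". Under Measurement, "the primary outcome will be walking capacity measured as the distance covered during the 6-minunte walk test at 12 months".

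Under Statistical analysis, the variables for walking capacity, quality of life and participation "will be analysed by pairwise comparisons between the three groups using the Students' t-test, or Wilcoxon's rank-sum test", the latter when the data are clearly not normal. That section names no covariate, no pooling of A and B, and no visit at which these tests apply.

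**The concern.** At month 2 the trial has, as assigned, two kinds of participant: those given two months of training (A and B) and those given none (C). Separate tests of A v C and B v C estimate the same training effect twice, each time with half of the trained participants. An A v B test at that visit compares identical assignments, so a significant result could be misread as an effect of duration.

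The later comparisons, including 4 v 2 months at 12 months, are also planned as plain two-sample tests. They make no use of the 6-minute distance measured at entry. In both places the trial would pay for precision that it already holds in its own data.

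**Working it through.** **Inputs.** From Sample size: difference 50 m, SD 100 m, 63 per group, two-sided 5%, 80% power, 10% dropout. The correlations between visits are not in the document. Every value used below is an assumption.

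**1. The plan's own figure.** n per group = 2 × (1.960 + 0.842)² × 100² / 50² = 62.8, rounded up to 63. Three groups give 189, and 189 / 0.9 = 210. All three figures reproduce. Power at 63 per group is 80.1% by the normal approximation and 79.5% by the noncentral t.

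**2. Month 2, one trained arm v C.** SE = 100 × √(1/63 + 1/63) = 17.8 m. The difference detectable with 80% power is 49.9 m.

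**3. Month 2, A+B v C.** SE = 100 × √(1/126 + 1/63) = 15.4 m. The ratio to step 2 is √0.75 = 0.866, a fall of 13%. Power for 50 m is 90.0% (noncentral t: 89.7%), and the detectable difference is 43.2 m. If all 70 per group attend, the SE goes from 16.9 to 14.6 m and power from 84.1% to 92.7%, the same proportional gain.

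**4. Month 2, A v B.** With no assigned contrast and no other source of difference, each test rejects 5% of the time. That is simply the nominal level. The difficulty is that the result has no meaning as a duration effect.

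**5. Later visits, adjustment for the entry value.** With correlation r between the entry and later distance, SE = 17.8 × √(1 − r²):

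| Assumed r | SE (m) | Power for 50 m |
|---|---|---|
| 0 (as planned) | 17.8 | 80.1% |
| 0.3 | 17.0 | 83.7% |
| 0.5 | 15.4 | 90.0% |
| 0.7 | 12.7 | 97.6% |

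**6. A v B at 12 months, adding the 2-month value to the entry value.** Residual variance is 1 − R², where R² = (a² + b² − 2abc) / (1 − c²), with a = entry–12 months, b = 2–12 months, c = entry–2 months.

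- 0.6/0.6/0.8: R² = (0.36 + 0.36 − 0.576) / 0.36 = 0.40. SE ratio to entry adjustment alone = √(0.60 / 0.64) = 0.97, a fall of 3%.
- 0.6/0.7/0.8: R² = (0.36 + 0.49 − 0.672) / 0.36 = 0.494. Ratio = √(0.506 / 0.64) = 0.89, a fall of 11%.
- 0.7/0.8/0.8: R² = (0.49 + 0.64 − 0.896) / 0.36 = 0.65. Ratio = √(0.35 / 0.51) = 0.83, a fall of 17%.

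The further gain from the 2-month value is therefore anywhere from slight to useful, depending on correlations that the document does not give.

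**The case against.** **The analysis section names no visit.** A reader might infer that the plan tests A v B at every visit. The text does not say so. The primary outcome is fixed at 12 months, and the month-2 visit also supplies the end-of-programme walking speed that the threshold analysis needs for Group B. This stands. Application at month 2 is the natural reading of a rule with no exception, but it remains a reading.

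**The A v B contrast at month 2 may not be exactly null.** A reader might infer that any significant difference there must be a false positive. That would need identical delivery and no effect of knowing the planned duration. The article refers to progression guidelines that it does not show, and describes a staged progression without saying whether pacing is the same in both arms. Allocation is made at entry, and only the researcher who collects and analyses the data is described as blinded. This also stands: what is the same is the assigned programme as described, and pooling carries an assumption.

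**Adjusting for the 2-month value could bias A v B.** It is tempting to treat that value as a second baseline whose use is free of bias. It is measured after randomisation. If pacing, expectancy or early dropout differed between A and B, conditioning on it would distort the 12-month contrast, whereas the unadjusted test is not exposed to this. Part of its gain also duplicates entry adjustment. The objection is good enough to keep this adjustment out of the main analysis.

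**The planned tests are valid, and a condensed article leaves model detail to the SAP.** The first part is right: the 63, 189 and 210 are correct. The second part is weaker, because the article does not leave the method open. It names unadjusted pairwise tests.

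**Conclusion.** The point holds as one of efficiency, not validity: a cheap improvement. Its firmest part needs only the document's own SD and group size. Pooling A and B at month 2 cuts the SE of the training effect by 13% and lifts power for 50 m from about 80% to 90%, provided that delivery to month 2 is the same in both arms. Pooling at month 2 does not by itself sharpen the 4 v 2 month comparison at 12 months. That gain comes from covariates.

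Adjustment for the entry value improves every later comparison to an extent set by an unstated correlation. Adding the 2-month value for A v B would reduce the SE by a further 3% to 17% under the assumed correlations shown, and only if there is no expectancy, pacing or early-dropout difference before month 2. The documents do not support the stronger conclusions that the planned tests are wrong or that the trial is underpowered for its stated 50 m.

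**What to change.** Amend the Statistical analysis section:

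1. At 2 months, make A and B pooled v C the comparison that estimates the training effect. State the assumption that delivery to month 2 is the same in both arms. Show A v B at this visit only as a check of that assumption, not as an effect comparison.
2. At 4, 6 and 12 months, adjust all pairwise comparisons of 6-minute distance for the entry value, by ANCOVA or a repeated-measures model.
3. Optionally, prespecify a sensitivity analysis of A v B only that also adjusts for the 2-month value. Exclude that covariate from comparisons with C, because training has already affected it.

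The cost is wording: every measurement is already scheduled, and the sample size need not change. The downside is the added assumption. Participants or therapists may know the planned duration, so pooling and 2-month adjustment both rely on there being no difference in expectancy, pacing or early dropout between A and B before month 2.
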